**Assessments / Tools**							
Demographics & Clinical Characteristics			X				
Physical Function (Resting HR, BP, O2sat, 6MWT, 30-s Sit-to-Stand)			X	X	X		
Health-related Quality of Life (EORTC QLQ-30) questionnaire			X	X	X	X	
Anxiety & Depression (HADS) questionnaire			X	X	X	X	
General Physical Activity (IPAQ-SF)			X	X	X	X	
Dietary Intake (MEDAS) questionnaire			X	X	X	X	
Mood (Daylio app)			X	X	X	X	
Sleep Quality (Daylio app)			X	X	X	X	
Participant Satisfaction, Diet, Exercise behaviour, Intent Feedback Surveys					X	X	
Parkrun event Adherence					X	X	
INTERVENTIONS:							
Parkrun participation					X		

This protocol describes a single group cohort study with participants acting as their own controls [23]. The study outline and timeline is shown in Fig. 1.

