Sample size was determined via simulation methods using a random intercept model with the R package [35]. We were interested in powering the study to detect changes in exercise adherence (measured as the proportion of cancer patients meeting minimum physical activity guidelines) and used this outcome variable in simulations. Data used to create the model were informed by previous studies [8, 10]. We assumed the average proportion of cancer patients meeting minimal physical activity guidelines for aerobic exercise was 30% [37]. Time (three levels- baseline, 6-months parkrun and follow-up), body mass index (BMI) and sex (two levels- male and female) were included as fixed factors within the sample size model. A random intercept was included for each individual participant. BMI and sex were included as fixed factors as these variables can influence exercise adherence in cancer patients [8–10]. Calculations were made assuming fixed effects of 6%, 30% and 5% for sex, time and BMI respectively, and a standard deviation of the random intercept of 2%. Based on these assumptions and a type I error rate of 5%, 80 participants give approximately 80% power to detect the specific time effect of 30% increase in the proportion of participants meeting physical activity recommendations. A minimum of 100 participants will be recruited, which even allowing for potential attrition of 20 participants would still provide a minimum sample size of 80.

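### The stated 80% power at 80 participants does not follow from the stated inputs: power is about 98% if the 30% increase is absolute and about 22% if it is relative

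*Protocol article*

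**What the plan says.** All of this is in the protocol article, under *Statistical analyses, sample size and power calculation*.

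- The study is powered on exercise adherence, "measured as the proportion of cancer patients meeting minimum physical activity guidelines".
- Starting level: "We assumed the average proportion of cancer patients meeting minimal physical activity guidelines for aerobic exercise was 30" per cent.
- Simulation model: a random intercept per participant, with time, sex and BMI as fixed factors. Time enters as "Time (three levels- baseline, 6-months parkrun and follow-up").
- Sizes: "fixed effects of 6%, 30% and 5% for sex, time and BMI respectively, and a standard deviation of the random intercept of 2" per cent.
- Result at a 5% type I error: "80 participants give approximately 80% power to detect the specific time effect of 30% increase in the proportion of participants meeting physical activity recommendations". The recruitment target of 100 is this 80 plus an allowance of 20 for attrition.

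The study is described under *Assessments / Tools* as a "single group cohort study with participants acting as their own controls", so all 80 people contribute to every time point.

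**The concern.** The paragraph gives enough inputs to check its own result. Each person either meets the guideline or does not, so the variance at each time point is fixed by the proportion. Once baseline, effect and n are given, little is left free to bring the power to 80%.

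The size of the effect is also ambiguous. An increase of 30% from a base of 30% can mean 60% (30 points) or 39% (a relative rise of 30%). The two readings lead to opposite conclusions about whether 80 is enough.

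This calculation is the only justification given for 80 and 100 participants. As written, a reader cannot tell what change in guideline adherence the study was able to detect, which matters most if no clear change is found.

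**Working it through.** **Inputs from the protocol article.** Baseline p1 = 0.30; p2 = 0.60 (absolute) or 0.39 (relative); n = 80, all measured at each time point; type I error 5%; random-intercept SD 0.02; sex 6%; BMI 5%.

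**Assumptions made here.** Two-sided test (sidedness is not stated); BMI effect taken per SD.

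**Step 1: the correlation implied by the 2% SD.**
0.02² / (0.02² + 0.30 × 0.70) = 0.0004 / 0.2104 = 0.0019. Repeated measurements on one person are treated as practically independent.

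**Step 2: power for 6 months versus baseline.**
Variance of one person's change: V = p1(1 − p1) + p2(1 − p2) − 2ρ√[p1(1 − p1)p2(1 − p2)]. Then z = (p2 − p1)/√(V/n), and power ≈ Φ(z − 1.96). With ρ = 0:

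| Reading | V | z | Power at n = 80 | n for 80% power, 2.80² × V/(p2 − p1)² |
|---|---|---|---|---|
| 30% to 60% | 0.21 + 0.24 = 0.450 | 0.30/0.0750 = 4.00 | 98% | about 40 |
| 30% to 39% | 0.21 + 0.2379 = 0.448 | 0.09/0.0748 = 1.20 | 22% | about 434 |

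The usual two-proportion formula agrees: 97.4% and 22.2%, with 42 and 437 needed per time point.

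**Step 3: simulation of the stated model.** Binary outcome, three time points, stated sex, BMI and intercept values, 3,000 runs per scenario.

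- 30% to 60%, held at follow-up: 97.9% for the 6-month contrast, 97.3% by McNemar's test, 98.9% for the overall time test. Other follow-up patterns give 94–99% for the overall test.
- 30% to 39%: about 21–24% for the 6-month contrast, and 17–21% for the overall test.
- 30% to 60% with n = 40: 79–81%.

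**Step 4: the effect that does have 80% power at n = 80.** Solving Step 2 for p2 gives a rise of 21 points at ρ = 0, 19 points at ρ = 0.2 and 16.5 points at ρ = 0.4. The 30-point and 9-point readings lie on either side of this range.

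**Step 5: attempts to reach the plan's 80%.**

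| Variant | 30% to 60% | 30% to 39% |
|---|---|---|
| One-sided 5% | 98.9% | 32.7% |
| Bonferroni over three contrasts | 93.2% | 11.5% |
| ρ = 0.2 | 99% | 27% |
| ρ = 0.4 | above 99% | 34% |
| Most favourable feasible ρ to the stated 80% | 85% (ρ = −0.80) | 80% (ρ = 0.82) |

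In the last row, a random intercept cannot produce the negative correlation, and 0.82 contradicts the stated 2% SD. Reading the 30% as a log-odds shift of 0.30, or as an odds ratio of 1.3, gives 12–14%.

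Two other routes come close. Treating 80 as two independent groups of 40, 30% versus 60%, gives 78%. A 30% relative rise repeated at each step (30%, 39%, 50.7%), tested as a linear trend, gives about 77%. Neither fits the text, which has one group, time as a three-level factor and a single 30% increase.

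**The case against.** The strongest reply is that the calculation was a simulation whose code and residual SD are not printed, and an article may leave such detail to the full protocol. The planned analysis is a linear mixed model with normal errors, so the simulation may have used a free residual SD. That is fair as to the source of the 80%, which cannot be established. It does not rescue the figure. For 80% power at n = 80 the residual SD would have to be 0.30/(2.80 × √(2/80)) = 0.68 on the absolute reading, above the maximum of 0.5 for a yes/no outcome. On the relative reading it would have to be 0.09/(2.80 × √(2/80)) = 0.20, less than half the 0.46–0.49 that proportions of 0.30–0.39 imply.

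A second reply is that the 30% stands beside 6%, 5% and 2% in one linear model and so most naturally means percentage points. The error is then on the safe side, since 80 is more than enough. The reading is plausible, but the closing phrase, "specific time effect of 30% increase in the proportion of participants meeting physical activity recommendations", does not exclude a relative rise, and 80% is wrong on both.

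A third reply is that the primary objectives are acceptability and adherence to parkrun, that 100 participants also serve those aims, and that a null result will be judged mainly by its confidence interval. This limits the practical harm. It does not make the stated power correct.

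Finally, the 2% intercept SD is a doubtful assumption and not an arithmetic slip. Agreed: a larger positive correlation would raise the power of the within-person comparison, so it cannot explain a lower figure on the absolute reading.

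**Conclusion.** The concern holds. With the stated inputs, 80 participants give about 98% power for 30% to 60% (97–99% across tests when the rise is held to follow-up) and about 22% for 30% to 39%. The stated 80% matches neither; at n = 80 it corresponds to a rise of about 21 points. On the first reading the sample is about twice what the stated effect needs (about 40). On the second it is less than a fifth (about 434).

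This rests on a yes/no outcome per person, a two-sided 5% test and the near-zero correlation that the 2% SD implies. Sidedness, multiplicity, follow-up pattern and any within-person correlation compatible with the stated model leave the conclusion unchanged.

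**What to change.** Keep the sample size and correct the paragraph.

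1. State whether the 30% is percentage points or relative.
2. Replace the 2% random-intercept SD with a stated range of within-person correlation, and name the contrast tested, its sidedness and the residual variance used.
3. Rerun the simulation and restate the power. If percentage points were meant, suitable wording would be: 80 participants give about 98% power for a rise from 30% to 60%, and 80% power for a rise of about 16 to 21 points (within-person correlation 0.4 to 0). The range 0 to 0.4 is an assumption of this review; the authors should substitute one they can support.
4. If a relative increase was meant, say that power is about 22% and do not present the study as powered for that change.

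The cost is a rewritten paragraph and a short simulation. Enrolment does not change.

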### Data management

All data will be given a numerical ID (parkrun ID number) and will be de-identified prior to any analysis. Participant contact details will be kept confidential and used only for points of contact regarding project enolment, data collection appointments and emailing/posting of paperwork. Participant details will only be available to the research team.

[name] will be in charge of data management. Electronic data will be stored in a project-specific, password-protected external hard drive and all backed up, de-identified data will be stored on the protected USC R drive. Any written material will be locked in a filing cabinet in the lead researcher’s office. We plan to make de-identified data and analysis code available in public repositories. All data will remain confidential and will be not identifiable for purposes of statistical analyses and publication. Coded data from each participant will be used for quantitative and qualitative anlyses. De-identified data and analysis codes can be made available to external researchers upon email request to the lead researcher. All data will be stored for a minimum of 5 years from the completion of the research as per university research guidelines and procedures. After archiving for a minimum of 5 years, any hard copy material may be shredded using contracted service providers. Project progress will be monitored throughout the duration of the study, with annual reporting to the USC Human Ethics Committee, and with monthly reporting to the research team members and project advisors.

### Dissemination

Deidentified study results will be published in peer-reviewed journals and at appropriate conferences. Summarized study results will also be sent to participants and to interested cancer-support organisations. A summary report will also be sent to the United Kingdom parkrun organization, who approve for any international parkrun research and request a summary of final results for publication on their website. If the research team receive external funding, a summary report will need to be sent the funding organization as part of the funding agreement.

## Discussion

Regular physical activity for people living with and beyond cancer, including aerobic, strength and other modes of exercise, are strongly recommended by oncologists, medical practitioners and exercise professionals. Exercise is regarded as an adjuvant treatment for cancers and can reduce some symptoms and treatment side effects. However, the majority of cancer survivors are not meeting recommended levels of exercise. The reasons are still unclear, are likely to be varied, and require further research. To improve strategies for exercise adherence, we need to understand more about patient enjoyment and acceptance of exercise modalities, and potential barriers to exercise participation. Previous studies have noted that group and community-based exercise programs can be successful because they provide a social framework and support, and companionship. This study will investigate the feasibility of using parkrun, an existing free group walk-run event, to engage cancer survivors in regular, self-paced walking or jogging.

### Limitations

The study has several strengths and limitations. Advantages include the use of an existing exercise program that has no direct costs, is easily accessible, is outdoors, and is supportive and safe in nature. The study will comprehensively profile participants and will have quantitative and qualitative outcome measures, participants’ experiential data and follow-up surveys. Limitations include the lack of randomisation and inclusion of participants with different types and stages of cancers. However, using a heterogenous sample is useful from the perspective of real-world clinical practice. As a feasibility study, this trial aims to identify benefits and barriers that affect parkrun participation and participant enjoyment and acceptance, and to lead to a larger longitudinal study.

## Data Availability

Datasets to be analysed in the study will be available from the corresponding author on reasonable request.

## Abbreviations

ADL: activities of daily living
PA: physical activity
HRQoL: health-related quality of life
PCOC: Palliative Care Outcomes Classification
FVC: forced vital capacity
BMI: body mass index
6MWT: Six Minute Walk Test
RPE: rate of perceived exertion
EORTC QLQ-30: European Organization for Research and Treatment of Cancer Quality of Life Questionnaire
HADS: Hospital Anxiety and Depression Scale
IPAQ-SF: International Physical Activity Questionnaire Short Form
MEDAS: Mediterranean Diet Adherence Screener
